## Abstract

**Background:**

About 20% of patients with primary breast cancer develop metastatic disease during the course of the disease. At this point the disease is considered incurable and thus treatment is aimed at palliation and life prolongation. As many patients will have received both an anthracycline and a taxane in the adjuvant setting, treatment options for metastatic breast cancer are limited. Furthermore response rates for the most commonly used drugs range from around 30% to 12% . Thus new treatment options are needed and preferably coupled to biomarkers predictive of response. Irinotecan is a topoisomerase 1 inhibitor used for decades for the treatment of colorectal cancer. Four studies have investigated the efficacy of irinotecan monotherapy in breast cancer and all have included non-biomarker selected patients. In these studies response rates for irinotecan ranged from 5%-23% and are thus comparable to response rates obtained with drugs commonly used in the metastatic setting. If a predictive biomarker could be identified for irinotecan, response rates might be even higher.

**Methods/Design:**

This multi-centre phase II single arm trial was designed to investigate if patients with metastatic breast cancer and increased expression of the topoisomerase 1 gene have a high likelihood of obtaining a clinical benefit from treatment with irinotecan. Trial recruitment is two-staged as 19 patients are planned to participate in the first part. If less than 7 patients have clinical benefit the trial stops, if more than 7 patients have clinical benefit a total of 40 patients will be included.

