#### Statistics

Number of patients in the study is based on Simon’s two-stage minimax design. Intention-to-treat analysis will be performed. By using a significance level of 0.05 (a = 0.05) and a power of 80% (b = 0.20) 19 patients should be included in the first step in order to find a CBR of at least 30%. Further inclusion ceases if less than 7/19 patients show CB. If 7 or more show CB another 20 patients will be included. If more than a total of 16 patients achieve CB the hypothesis is satisfied.

PFS and OS will be estimated using the Kaplan-Meier method and compared with a log-rank test. Categorical variables are indicated by a median followed by the span. A significance level of 5% will be used. PFS and OS will be assessed in the evaluable population.

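### The abstract gives a total of 40 patients and no action at exactly 7 of 19; the Statistics section, which reproduces the stated design, continues at 7 or more to a total of 39

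*Protocol article*

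**What the plan says.** The two-stage rule appears twice in the protocol article.

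- **Abstract, Methods/Design paragraph.** "Trial recruitment is two-staged as 19 patients are planned to participate in the first part". The trial stops if fewer than 7 have clinical benefit, and "if more than 7 patients have clinical benefit a total of 40 patients will be included". No final success cut-off is given.
- **Methods/Design, Statistics.** "Number of patients in the study is based on Simon’s two-stage minimax design". Alpha is 0.05 and power 80%. The stopping rule is "Further inclusion ceases if less than 7/19 patients show CB", the continuation rule is "If 7 or more show CB another 20 patients will be included", and the final rule is "If more than a total of 16 patients achieve CB the hypothesis is satisfied".

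The only rate attached to the calculation is in the phrase "in order to find a CBR of at least 30" per cent. The section does not label it as the null rate, and it states no target rate.

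**The concern.** The two places differ in two respects.

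1. **Total.** The abstract says 40. The Statistics section implies 19 + 20 = 39.
2. **Exactly 7 of 19.** The abstract covers fewer than 7 and more than 7, and is silent at 7. The Statistics section continues at 7.

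These are the go/no-go boundary and the final denominator of the primary analysis. In an exact binomial design the success cut-off belongs to one particular sample size and stage-1 boundary, so changing either one alters the error rates. The Trial status section reports 10 patients included, so the stage-1 decision still lay ahead. If 7 of 19 had been observed, or a fortieth patient enrolled, the two texts would have left room to choose the rule with data in hand.

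**Working it through.** **Inputs**

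- From Statistics: n1 = 19; stop at r1 = 6 or fewer; n = 19 + 20 = 39; success if the total exceeds r = 16; alpha 0.05; power 0.80.
- From the abstract: n = 40; continuation worded as above 7.
- Null rate p0 = 0.30. This is the only rate stated, and reading it as the null is an interpretation.
- Target rate p1 = 0.50. **This is an assumption; the document gives no target.**

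**Formula**

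P(success | p) = sum over x > r1 of P(X1 = x) × P(X2 ≥ r + 1 − x), with X1 ~ Bin(19, p) and X2 ~ Bin(n − 19, p). Alpha is this at p0, power is this at p1.

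**Step 1: reproduce the plan's design.** A full minimax search at alpha ≤ 0.05 and power ≥ 0.80 gives:

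| p0 / p1 | minimax design (r1/n1, r/n) |
|---|---|
| 0.10 / 0.30 | 1/15, 5/25 |
| 0.15 / 0.30 | 3/23, 11/48 |
| 0.20 / 0.40 | 4/18, 10/33 |
| 0.30 / 0.50 | 6/19, 16/39 |

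Of the pairs tried, only 0.30/0.50 returns the Statistics design. Its alpha is 0.0455 and its power 0.8036, so both stated limits are met.

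**Step 2: vary the rule.** Success is above 16 throughout, because that is the only cut-off in the document.

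| Continue at | n | alpha (p = 0.30) | power (p = 0.50, assumed) |
|---|---|---|---|
| 7 or more (Statistics) | 39 | 4.55% | 80.4% |
| 7 or more | 40 | 5.62% | 83.1% |
| 8 or more | 39 | 3.82% | 74.7% |
| 8 or more | 40 | 4.59% | 76.7% |

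Two of these can be checked by hand:

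- *Effect of the fortieth patient on alpha.* It changes the result only if the trial continued and stands at exactly 16 of 39, and that patient then benefits. At p = 0.30 the first event has probability 0.0356, so alpha rises by 0.0356 × 0.30 = 0.0107, and 0.0455 + 0.0107 = 0.0562.
- *Effect on power of not continuing at 7 (n = 39).* The loss is P(X1 = 7) × P(X2 ≥ 10 of 20). At p = 0.50 this is 0.0961 × 0.5881 = 0.0565, and 0.8036 − 0.0565 = 0.7471.

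**Step 3: can 40 be rescued by another final cut-off?** With n = 40, continuing at 7 or more and requiring more than 17 gives alpha 2.97% and power 76.3%. Across all stage-1 boundaries and final cut-offs with 19 then 40 patients, none meets both limits at 0.30/0.50.

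**Step 4: sensitivity to the assumed target.** Power when continuing only at 8 or more, success above 16:

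| p1 | n = 39 | n = 40 |
|---|---|---|
| 0.50 | 74.7% | 76.7% |
| 0.51 | 78.1% | 79.8% |
| 0.52 | 81.2% | 82.7% |

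**Step 5: how often the gap matters.** P(X1 = 7) = C(19,7) p^7 (1 − p)^12, which is 15.3% at p = 0.30 and 9.6% at p = 0.50.

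**The case against.** The strongest reply is that the detailed design text is right and complete. The Statistics section gives a stop rule, a continuation rule, a stage-2 size and a success cut-off that fit together and meet the stated limits. Someone running the trial from it would make no error. This stands, and it limits the severity.

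Two stronger readings are tempting, and the documents do not support either.

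- **A reader might infer that the two texts have opposite stage-1 rules.** They do not. Both stop only below 7. At exactly 7 the abstract is silent, which is a gap that the Statistics section fills. The power figures of 74.7% and 76.7% apply only if someone resolved that silence by stopping at 7, which neither text instructs.
- **A reader might infer that following the abstract in itself breaks the 5% level.** The abstract has no success cut-off, so no alpha follows from it alone. The 5.6% combines its total of 40 with the continuation rule and cut-off of the Statistics section. With 40 patients, the same cut-off and continuation only above 7, alpha is 4.6%, inside the limit.

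The power shortfalls also rest on an unstated target. With 40 patients, continuing only at 8 or more, power is about 80% at a target of 51% and 83% at 52%.

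It may also be said that 40 is merely 39 rounded. That is possible, but the abstract states it as the number to be included. At the inferred rates no cut-off makes 19 then 40 meet both limits.

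**Conclusion.** The inconsistency is real, of moderate importance, and confined to the abstract. The totals of 40 and 39 contradict each other, and exactly 7 of 19 is unassigned in one text and means continue in the other. The Statistics section is the coherent version.

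The consequences are conditional. Enrolling 40 under the Statistics rules would put alpha at 5.6%, an excess of 0.6 percentage points; this figure needs only the 30% null. Treating exactly 7 as insufficient would cost 80.4 − 74.7 = 5.7 points of power with 39 patients, or leave it 80.4 − 76.7 = 3.7 points lower with 40. Both power figures depend on the inferred 50% target. The unassigned outcome is not rare, at roughly one chance in seven under the null rate and one in ten at the assumed target.

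**What to change.** Correct the abstract to match the Statistics section: stop if 6 or fewer of the first 19 have clinical benefit; continue if 7 or more; 39 patients in total (19 + 20); success if 17 or more of 39. In the Statistics section, label 30% as the null rate if that is what was meant, and state the target rate used (50% if the inference here is right).

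Do not plan to handle a fortieth patient by testing only the first 39 enrolled. That would leave an enrolled patient out of the primary test, in conflict with the intention-to-treat analysis the Statistics section announces.

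The cost is wording only. The design in the Statistics section does not change, and the total is one patient fewer than the abstract states.

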**Discussion:**

This ongoing trial is the first to prospectively test copy number of the topoisomerase I gene as a predictive biomarker of response to irinotecan.

**Trial registration:**

EudraCT number 2012-002348-26.

## Background

Breast cancer (BC) is the most common malignancy among women in the western world. Despite improvements in the adjuvant treatment around 20% of patients with primary BC will develop recurrence [1]. Metastatic breast cancer (mBC) is considered incurable in the vast majority of cases and thus treatment is aimed at palliation and life prolongation. Depending on estrogen (ER) and human epidermal receptor 2 (HER2) status, treatment options include a handful of cytostatic drugs among which the anthracyclines and the taxanes are the most efficient. Given as first-line treatment to chemo-naïve patients, anthracyclines have shown response rates (RR) of up to 70% [2,3]. Among patients exposed to adjuvant non-anthracycline containing chemotherapy RRs are around 50% [2,4,5], while these figures drop to around 36%-38% when given to patiets previopusly treated with anthracyclines in the adjuvant setting [6]. Taxanes have shown RRs of approximately 40% in the first-line setting [7,8], dropping to 26-30% as second-line treatment [9]. The proportion of patients with primary BC receiving some kind of adjuvant therapy has increased during the past 20 years. Although not all patients receive adjuvant chemotherapy still a growing number of patients will have been exposed to both anthracyclines and taxanes at the time of recurrence. In these cases or following relapse on either treatment capecitabine or vinorelbine will often be considered as rational treatment options. Although no specific recommendations are given in international guidelines regarding the choice of drug for second- or third line treatment, unanimously guidelines recommend sequential monotherapy [10,11]. Capecitabine has shown RRs in the range 20% to 30% as first-line treatment [12-15] and vinorelbine has showed RRs of 15%-25% when given as second- or third line treatment [16-18]. Eribulin a new microtubule inhibitor has shown RRs of 12% in heavily pre-treated patients whereas the old drug gemcitabine is effective in 20% to 37% of patients depending on line of treatment [19-22]. From these figures it is evident that the majority of patients are deriving no benefit from treatment with these agents but nevertheless suffer the associated side effects. New individualized treatment options are needed for these patients. In order to improve the therapeutic index, preferably all drugs should be coupled to biomarkers predictable of response to the treatment. This is already in use with anti-ER and anti-HER2 treatments but for the cytotoxic chemotherapeutics no such biomarkers are developed to a stage where they can be implemented in daily clinical breast cancer management.

### Irinotecan

Irinotecan is a topoisomerase 1 (Top 1) inhibitor acting as a pro-drug and is enzymatically converted to the active metabolite SN-38 [23]. Like other Top 1 inhibitors it exerts its mechanism of action through binding to the Top 1-DNA complex during replication and transcription and thereby maintaining single-strand DNA breaks, ultimately resulting in the formation of double-stranded DNA breaks, which causes cell death [24]. Irinotecan has been used in the treatment of colorectal cancer (CRC) for decades. Several studies have tried to establish a correlation between expression of the *TOP1* gene or protein and response to irinotecan. Results have been conflicting and study methods have varied significantly making comparisons of the various studies quite difficult. Today no standardized methods for detecting Top 1 protein expression have been established and no validated scoring systems exists for neither gene nor protein expressions. Nevertheless, some studies have found a correlation between *TOP1* gene as well as protein expressions and response to irinotecan [25,26]. From our laboratory, we have published a significant correlation between *TOP1* gene copy number and sensitivity to SN38 in 10 human CRC cell lines [27] and very recently we published on the association between *TOP1* gene copy number and benefit from irinotecan treatment in metastatic CRC [28]. These studies suggest that *TOP1* gene copy number determinations can be used as predictive biomarker for irinotecan treatment in CRC patients. However, additional clinical studies are need to establish *TOP1* gene copy number as an irinotecan predictive biomarker in CRC patients and further as a predictive biomarker for irinotecan treatment of BC patients.

### Irinotecan in BC

Few studies on irinotecan in BC have been published. A systematic review identified 19 trials [29]. No phase III or randomized phase II trials have been published except for trials randomizing between different dosing schedules of irinotecan monotherapy [30,31] and only one study included more than 100 patients [30]. All trials included unselected patients and prior treatment with an anthracycline and/or a taxane was required in all but one study. Four studies investigated irinotecan as monotherapy. Treatment schedules varied among the studies as three studies investigated intravenous irinotecan given either weekly for 4 weeks followed by two weeks break, given every other week or given every third week [30,32,33]. The last study investigated oral irinotecan [31]. RRs ranged from 5% to 23% with the higher response rate found in a study by Perez et al. in which two different schedules of irinotecan were compared [29]. One hundred and three women were included and a maximum of two prior treatment regimens for mBC was allowed. Patients received either weekly irinotecan for four weeks followed by two weeks break (q 42d) or irinotecan every 3 weeks (q 21d). RR in the q 42d arm was 23% (CI 13%-37%) compared to 14% (CI 6-26%) in the q 21d arm. Median response duration was 4.9 months for patients in the q 42d arm compared to 4.2 in the q 21d arm and median OS was 9.7 months (CI 8.0-14.2 months) and 8.6 (CI 7.0-12.3 months), respectively [30]. The two remaining studies on intravenously irinotecan both showed RR of approximately 6% [32,33]. However, one study was a retrospective study of 20 patients previously treated with both an anthracycline and docetaxel [33] while the other study included 18 patients of which 72% had received three or more chemotherapy regimens for metastatic disease [32]. The last study was on oral irinotecan [31]. A more recent study investigated the new polymer conjugate of irinotecan; etirinotecan (NKTR-102). A total of 70 patients were included with a maximum of two prior treatment regimens for metastatic disease. Etirinotecan was administered every 14 days (q14d) or every 21 days (q21d). Progression free survival (PFS) was 3.5 months in the q14d arm and 5.3 months in the q21d arm and overall survival (OS) was 8.8 months and 13.1 months, respectively. However, the RR of 32% was superior in the q14d arm compared to the RR of 26% in the q21d arm [34]. Thus RRs for irinotecan are comparable to those found for taxanes used in second-line and to vinorelbine, gemcitabine and eriblulin used in second- or later lines of treatment. However, as all of the previously conducted studies with irinotecan in BC have included unselected patients, the RR for irinotecan could possibly be higher if a biomarker for response could be identified.

### Topoisomerase 1 in BC

In order to make TOP1 a clinically relevant biomarker for response to irinotecan, overexpression of the protein would have to occur in a fairly large part of patients. Only one published study has investigated the frequency of Top 1 protein expression in BC. A small study including samples from 22 primary BC reported increased expression of Top 1 by immunohistochemistry (IHC) in 41% of the investigated samples indicating that this aberration is quite common in BC [35].

Conclusively, the available data on irinotecan for the treatment of mBC are very scant and insufficient but they all point to a potential role of this drug in treatment of mBC patient with prior taxane and anthracycline treatment. An objective RR to irinotecan treatment in such patients appears to be approximately 25-30% and therefore calls for identification of irinotecan predictive biomarkers to avoid unnecessary drug induced site effects in non-responsive patients.

The aim of the below presented clinical study is to investigate if patients with mBC and increased gene expression of *TOP 1* in their cancer cells have a high likelihood of obtaining a clinical benefit when treated with irinotecan.

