#### Study objectives

The primary end point of this study is clinical benefit rate (CBR) defined as the fraction of patients receiving clinical benefit (CB) in the form of complete or partial response or stable disease ≥ 4 months according to RECIST 1.1. Secondary endpoints include PFS, OS and toxicity.

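### The article's summary irinotecan response rate (25-30%) exceeds its own cited 5-23%, and reaching 17/39 would show a CBR above 30%, not that TOP1 selection raises benefit

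*Protocol article*

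**What the plan says.** All places are in the protocol article.

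- **Abstract, Background**, on the four irinotecan monotherapy studies in unselected patients: "In these studies response rates for irinotecan ranged from 5%-23" per cent.
- **Irinotecan in BC** repeats the range, "RRs ranged from 5% to 23" per cent, and itemises it. For the largest study: "RR in the q 42d arm was 23% (CI 13%-37%) compared to 14% (CI 6-26%) in the q 21d arm". The two other intravenous studies "both showed RR of approximately 6" per cent. For etirinotecan, presented as a polymer conjugate of irinotecan: "the RR of 32% was superior in the q14d arm compared to the RR of 26% in the q21d arm".
- **Topoisomerase 1 in BC** then sums up: "An objective RR to irinotecan treatment in such patients appears to be approximately 25-30" per cent.
- **Study objectives** makes CBR the primary endpoint, counting complete response, partial response, or stable disease lasting at least 4 months. It adds: "Secondary endpoints include PFS, OS and toxicity". ORR is not named.
- **Statistics** specifies a Simon minimax design with alpha 0.05 and power 80%. The first 19 patients are included "in order to find a CBR of at least 30" per cent. Recruitment stops if fewer than 7 have benefit; otherwise 20 more enter, and more than 16 with benefit satisfies the hypothesis.

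**The concern.** The summary response rate and the evidence listed before it do not agree. The summary lies above every irinotecan point estimate in the article and resembles only the conjugate's figures.

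This matters beyond wording because the trial has one arm. Its only link to patients not selected on TOP1 is the historical evidence, and all the activity rates cited there are response rates. The benchmark is a CBR, a different and larger quantity. If unselected patients already have a CBR above 30%, the trial can pass without any contribution from the marker. The Abstract and the Discussion nevertheless present the trial as a test of TOP1 copy number as a predictive marker. At stake is what a positive result may be said to show.

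**Working it through.** **1. Response rates side by side**

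| Source in the article | Agent | RR |
|---|---|---|
| Range over four monotherapy studies | irinotecan | 5-23% |
| Largest study, q 42d arm | irinotecan | 23% (CI 13-37%) |
| Largest study, q 21d arm | irinotecan | 14% (CI 6-26%) |
| Two other intravenous studies | irinotecan | about 6% each |
| q14d and q21d arms | etirinotecan | 32% and 26% |
| Background summary | stated as irinotecan | 25-30% |

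**2. Reproducing the design**

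Let X be the number with benefit among the first 19 and Y the number among the next 20. For a true rate p,

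P(pass) = sum over x = 7 to 19 of P(X = x) × P(Y ≥ 17 − x), with X ~ Bin(19, p) and Y ~ Bin(20, p).

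An exact search for the smallest maximum sample size with alpha ≤ 0.05 and power ≥ 0.80 gives:

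- p0 = 30%, p1 = 50%: stop at ≤ 6/19, fail at ≤ 16/39; alpha 0.0455, power 0.804. This is the stated rule.
- 30% as the alternative: p0 = 10% gives 1/15, 5/25, and p0 = 15% gives 3/23, 11/48. Neither matches.

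So 30% works as the null rate, although the Statistics section words it as the rate to find. The alternative of 50% is inferred; the article does not state it. Success needs 17/39 = 43.6% observed.

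**3. Null CBR against the article's own RR**

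CBR = RR + s, where s ≥ 0 is the share with stable disease of at least 4 months. With RR = 25-30%, a 30% null leaves s = 30 − 30 = 0 to 30 − 25 = 5 points.

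**4. Probability of passing if the marker adds nothing**

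| True unselected CBR | P(pass) |
|---|---|
| 20% | 0.0006 |
| 25% | 0.008 |
| 26% | 0.012 |
| 30% | 0.0455 |
| 35% | 0.156 |
| 40% | 0.356 |
| 45% | 0.599 |
| 50% | 0.804 |

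**5. Conversion from RR**

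The article gives no value for s. Taking s = 10-20% purely as an assumption:

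| RR taken as true | CBR = RR + s | P(pass) |
|---|---|---|
| 6% | 16-26% | below 0.001 to 0.012 |
| 14% | 24-34% | 0.005 to 0.126 |
| 23% | 33-43% | 0.101 to 0.502 |
| 25% | 35-45% | 0.156 to 0.599 |
| 30% | 40-50% | 0.356 to 0.804 |

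Widening s to 5-25% gives 0.000 to 0.31 at RR 14% and 0.024 to 0.73 at RR 23%. The result depends mainly on two quantities the article does not settle: the RR and s.

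**The case against.** The strongest case against has five parts.

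- **The 25-30% is a loose Background summary.** The authors appear to pool irinotecan with its conjugate, and the 23% arm's interval (13-37%) covers 25-30%. Nothing says the design was derived from this figure. That stands as an explanation, and correcting the sentence alone would be close to clerical. It does not make the sentence right: an interval around the best arm does not support a summary above every point estimate.
- **The source of the 30% may be in the full protocol.** This stands. The article's silence is not evidence that 30% is wrong, and I do not claim that it is.
- **ORR is not the only comparable endpoint.** A reader might infer that nothing else can be set against history. The article also cites OS for irinotecan and PFS and OS for etirinotecan, and PFS and OS are listed endpoints. The wording of the secondary endpoint list does not make it exhaustive either, and ORR can be derived from data collected for CBR. What remains is narrower: ORR is the only response-type rate with a comparator in the article, and the rationale is argued in response rates.
- **The lower the true RR, the weaker the worry.** This stands. At RR 6% the chance of a pass without a marker effect is at most 0.012 under the assumed s of 10-20%. This trial allows up to 4 prior regimens for metastatic disease, against 2 in the largest earlier study, and in one of the 6% studies 72% had received three or more. The low end is therefore relevant here.
- **The stated aim is a high likelihood of benefit in selected patients,** which a one-sample test can address. True, but the Abstract and Discussion also use the language of prediction, which this design alone cannot support.

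**Conclusion.** The concern holds in a limited form. The 25-30% figure is unsupported by the irinotecan results in the same article. The design tests CBR against 30%, and on that 25-30% figure the null sits at or barely above the unselected response rate alone. Reaching 17/39 would therefore support a CBR above 30% in TOP1-increased patients; it would not by itself show that selection raised benefit.

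A reader might go further and infer that unselected activity would probably carry the trial over the line. The article does not support that. The probability is 0.0455 at an unselected CBR of 30%, as designed, and about 0.01 or less at 26% or below. It becomes large (0.36 and above) only from about 40%, which requires a stable-disease share the article does not give. Nor do the etirinotecan PFS times fill the gap: they come from a different agent, and turning them into a 4-month rate needs further assumptions about the curve.

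The point is worth acting on because the changes cost almost nothing and they govern what a positive result may claim.

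**What to change.** 1. In Topoisomerase 1 in BC, give 5-23% as the irinotecan response rate and report etirinotecan (26% and 32%) separately as a different agent.
2. In Study objectives, name ORR (CR + PR, RECIST 1.1) as a secondary endpoint with an exact 95% CI in all enrolled patients. Read it against the cited irinotecan rates (5-23% overall; 14-23% in the largest study), noting the difference in prior lines. The denominator matters, since Trial status reports two patients who withdrew before their first CT evaluation.
3. In Statistics and Discussion, state that 30% is the null on the CBR scale and limit a positive conclusion to CBR above 30% in TOP1-increased patients, without calling the marker predictive on this evidence. Printing the pass probabilities for a range of unselected CBRs is optional.

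Cost: no extra patients, scans or design change, because RECIST response is already recorded for CBR. The price is a more modest reading of a positive result. The ORR comparison will also be imprecise: at 23% and n = 39 the approximate half-width is 1.96 × √(0.23 × 0.77 / 39) = 0.13, or about 13 points, so it gives context and not a second test.
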